### Participants/eligibility criteria

The sample population will consist of women who sustain a primary post-partum haemorrhage in excess of 1000 mL with a resultant Hb drop of ≥3 g/dL and Hb of 5.5-8.0 g/dL. Asymptomatic women, as well as patients with mild signs and/or symptoms of anaemia including dizziness, increased respiratory rate to >/= 25 on minimal exertion, HR 100-130 or a postural blood pressure drop of >10 mmHg are eligible.

Blood loss will be assessed by weighing all blood stained articles including sponges, sheets, under-pads and clothing. If delivery occurs in the operating theatre (after subtracting liquor volume) suction output will be added. Where possible all blood spillage will be mopped up, weighed and added to the total.

Evidence suggests 90% of women with PPH > 1000 mL have resultant Hb < 10 g/dL thereby defining our haemorrhage cut off [1]. Similarly the nominated minimum Hb is a conservative estimate based on levels used in previous studies evaluating expectant management in patients with acute anaemia [6, 10, 11, 17].

If applicable, enrolment must occur within 48 h of resuscitation and stabilisation. Stabilisation is defined as (1) having no active per vaginal bleeding in excess of expected post-partum losses and (2) having all vital parameters within hospital review criteria for a period of 12 h immediately prior to study recruitment (i.e. all patients having pulse <130 bpm, systolic blood pressure > 90 mmHg, diastolic blood pressure < 110 mmHg, respiration rate < 25, temperature < 38.5 degrees and oxygen saturations >90%).

Patients with significant antenatal or peri-partum complications such as severe pre-eclampsia who are now stable (as per above criteria) are eligible. Women who receive whole blood transfusion, other blood products, antibiotics (other than for sepsis) and intravenous fluid therapy prior to stabilisation will also be eligible.

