### Major exclusion criteria

Age < 16 or >50 yearsRefuse consent to blood transfusion or iron infusionCo-morbidities necessitating rapid Hb restoration including: cardiac failure, ischemic heart disease, chronic renal failureKnown hematological malignancyKnown hemaglobinopathies requiring regular transfusionsSepsis (clinical or laboratory evidence—intrapartum fever >38.5 degrees with abnormal vital signs, positive blood culture)Contraindications to iron polymaltose (i.e. asthma, known hypersensitivity to iron polymaltose, chronic polyarthritis, acute renal dysfunction, uncontrolled hyperparathyroidism, infectious hepatitis and iron overload (ferritin >1000 ng/L)Severe symptoms of anemia including dyspnoea at rest, angina pectoris, syncope or transient ischemic attacks.

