### Interventions

All eligible women will be approached and given information about the intervention arms of the study ie. the blood transfusions and intravenous iron including details about the interventions themselves and other scientific and ethical considerations. Those who decline either intervention will be offered oral iron in line with standard practice. These women will be invited to participate in the trial as part of an oral iron subgroup which has an identical follow up protocol. Thse women will be administered 325 mg of oral iron daily. This is not a randomised arm of the study.

Patients in the intervention group will be randomised to receive cross-matched RBC transfusion or an IV iron polymaltose infusion. In patients allocated to RBC transfusion, Hb will be checked after each unit and given to achieve a Hb of at least 9.0 g/dL. Patients who received transfusions will be discharged on 325 mg of oral ferrous sulphate for a minimum of 4 weeks.

Iron poylmaltose was selected instead of iron carboxymaltose as it allows for individualised dose calculations and a larger dose of iron to be administered. Iron carboxymaltose, despite having a shorter infusion time, has a maximum of 1 g that can be administered within a 7 day period.

The dose of iron polymaltose will be calculated according to the Ganzoni formula: Total iron dose (mg) = body weight (kg) x (150-baseline Hb (g/dL)) × 0.24 + 500 mg, assuming a target Hb of 15.0 g/dL which allows for ongoing normal per vaginal loss during the puerperium. For those with Thalassemia minor, the target Hb will be adjusted to reflect the patients pre-pregnancy Hb. Iron will be administered as per hospital protocol which instructs slow infusion at 20-40 mL/h for the first 50 mL, increasing to 120 mL/h based on patient tolerance.

Patients will be pre-medicated with anti-histamine (10 mg cetirizine hydrochloride) and anti-emetic (metoclopramide 10 mg) 1 h prior to the iron infusion to reduce adverse reactions [18]. During the infusion patients will be monitored for adverse affects including itch and urticaria, bronchospasm/dyspnoea, back, joint or muscle pain, nausea, indigestion, abdominal pain, headache, hypotension, tachycardia, syncope, and circulatory collapse [9].

Any patient experiencing an adverse reaction will receive appropriate medical care including additional RBC transfusion if indicated. Infusion rates will be slowed in the instance of mild to moderate reactions and ceased for severe reactions.

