### Data collection

Each participant will have a study file labelled with their name, medical record number, study identification number and allocated treatment. This will contain copies of their consent forms (the original will remain in their hospital file while they are an inpatient), questionnaires and comprehensive study checklists template for documenting outcome variables and other clinical data. Files will be kept in locked cabinets on the ward and in the principle researcher’s office after discharge and remain on site for 7 years before being destroyed/archived.

Baseline blood results (Hb, ferritin, CRP) for all enrolled participants will be manually transcribed by researchers from the hospital electronic database into the participant’s study file. Once allocated to an intervention, the number and coding sticker of each blood unit or the serial number and dose of the pre-packaged iron infusion will be recorded in the template.

Patient symptoms will be scored on Day 0 prior to receiving any intervention using previously validated HRQoL questionnaires: the EuroQol-5D (E-5D), the Multidimensional Fatigue Inventory (MFI-20) and our in-hospital devised Post-Partum Symptom Score (PPSS).

The EQ-5D measures a patient’s activity level and emotional attitude at a single point in time, indirectly reflecting symptom severity. It consists of five items (Mobility, Self-Care, Usual Activities, Pain/Discomfort and Anxiety/Depression) where a patient scores: 1 = no problems, 2 = more problems, 3 = extreme problems. The sixth item is a patient’s own global evaluation of their health using a visual analogue scale with a range from 0 (worst imaginable health state) to 100 (best imaginable health state) [21].

The MFI is a 20-item self-report instrument designed to comprehensively measure fatigue. It evaluates: general, physical and mental fatigue and reduced motivation and activity. Patients score each dimension on a scale ranging from 4 to 20 where 4 is optimal. Hence, higher scores indicate more severe symptoms. Scales are balanced to reduce the influence of response tendencies. Each scale sub-total is interpreted independently. Questions are structured to evaluate symptoms over a period of time (5-7 days) which is particularly useful to measure treatment impacts [22]. Both the MFI and EQ-5D have previously been validated in pilot studies of obstetric cohorts [23].

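### The iron dose formula subtracts a haemoglobin in g/dL from a target in g/L; followed as printed, it overdoses by about 35–82% (assumed weights 45–120 kg)

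*Protocol article*

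**What the plan says.** The Interventions section of the protocol article gives the dose for the experimental arm as "Total iron dose (mg) = body weight (kg) x (150-baseline Hb (g/dL"; the bracket is then multiplied by 0.24 and 500 mg is added. The formula is described as "assuming a target Hb of 15.0 g/dL which allows for ongoing normal per vaginal loss during the puerperium".

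Three other statements bear on how it should be read:

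- Iron polymaltose was preferred because it "allows for individualised dose calculations and a larger dose of iron to be administered", whereas the carboxymaltose product "has a maximum of 1 g that can be administered within a 7 day period" (Interventions).
- "For those with Thalassemia minor, the target Hb will be adjusted to reflect the patients pre-pregnancy Hb" (Interventions). No unit is given for this adjusted target.
- Eligible women have a haemorrhage above 1000 mL, a fall in Hb of at least 3 g/dL "and Hb of 5.5-8.0 g/dL" (Participants/eligibility criteria). The transfusion target (Interventions) and the acceptable difference (Statistics) are also in g/dL.

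Separately, Major exclusion criteria lists "iron overload (ferritin >1000 ng/L" among the contraindications.

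**The concern.** A target of 15.0 g/dL equals 150 g/L. The printed formula therefore takes its target in g/L and its baseline Hb in g/dL, a tenfold mismatch inside one subtraction. Because the article reports Hb in g/dL, the figure a prescriber has at hand is 7.0, not 70, and the label on the formula tells them to enter it in that form.

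This rule sets a single infusion in the experimental arm. If a site or pharmacy follows it as written, two things happen. Women receive materially more iron than intended, and the part of the dose that should depend on Hb nearly disappears. Dose bears directly on Day 7 Hb and ferritin, both primary outcomes, and on adverse reactions. If some sites read the label literally and others silently correct it, the treatment under test differs between sites.

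**Working it through.** **Inputs from the protocol article.** Constants 150, 0.24 and 500 mg; target 15.0 g/dL (Interventions). Baseline Hb 5.5–8.0 g/dL (Participants/eligibility criteria). The article gives no worked dose, so there is no stated figure to reproduce.

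**Assumption.** Body weight w of 45, 70 and 120 kg. The article gives no weights.

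**Formulas** (Hb in g/dL throughout):

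- As printed: w × (150 − Hb) × 0.24 + 500
- Units made consistent: w × (150 − 10 × Hb) × 0.24 + 500, which equals w × (15.0 − Hb) × 2.4 + 500
- Alternative repair: w × (15.0 − Hb) × 0.24 + 500

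**Which repair is meant.** The alternative gives 45 × 7.0 × 0.24 + 500 = 576 mg at its lowest (45 kg, Hb 8.0) and 120 × 9.5 × 0.24 + 500 = 774 mg at its highest (120 kg, Hb 5.5). It never reaches 1 g, which contradicts the reason given for choosing the product. The consistent formula gives 45 × 70 × 0.24 + 500 = 1256 mg to 120 × 95 × 0.24 + 500 = 3236 mg, always above 1 g. So 150 is right and the Hb label is the slip.

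**Size of the error if the printed label is followed:**

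| Weight (kg) | Hb (g/dL) | As printed (mg) | Consistent (mg) | Excess |
|---|---|---|---|---|
| 45 | 5.5 | 2061 | 1526 | +35% |
| 45 | 8.0 | 2034 | 1256 | +62% |
| 70 | 5.5 | 2928 | 2096 | +40% |
| 70 | 7.0 | 2902 | 1844 | +57% |
| 70 | 8.0 | 2886 | 1676 | +72% |
| 120 | 5.5 | 4662 | 3236 | +44% |
| 120 | 8.0 | 4590 | 2516 | +82% |

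The absolute excess is w × 9 × Hb × 0.24 = 2.16 × w × Hb mg: 535 mg at 45 kg and Hb 5.5, 1058 mg at 70 kg and Hb 7.0, 2074 mg at 120 kg and Hb 8.0. The proportional excess is largest in the least anaemic women.

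**Loss of dependence on Hb.** At 70 kg, going from Hb 5.5 to 8.0 g/dL changes the printed dose by 70 × 2.5 × 0.24 = 42 mg. The consistent formula changes it by 70 × 25 × 0.24 = 420 mg. The printed dose still scales with weight.

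**Thalassaemia minor** (assumed 70 kg, Hb 7.0 g/dL, pre-pregnancy Hb 11.0 g/dL):

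- Intended: 70 × (110 − 70) × 0.24 + 500 = 1172 mg
- Both values entered in g/dL: 70 × (11 − 7) × 0.24 + 500 = 567 mg (−52%)
- Target in g/L, Hb in g/dL: 70 × (110 − 7) × 0.24 + 500 = 2230 mg (+90%)

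For assumed targets of 10.0 and 12.0 g/dL the intended doses are 1004 and 1340 mg. The first mistake gives 550 and 584 mg (−45% and −56%), the second 2062 and 2398 mg (+105% and +79%). In this subgroup the slip can err in either direction.

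**Ferritin.** 1000 ng/L is 1 microgram/L, which cannot identify iron overload.

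**The case against.** The best reply is that the sentence exposes its own mistake. It names the Ganzoni formula and states the target, the constants agree with each other, and only one unit label is wrong. Staff used to the formula with Hb in g/L would dose correctly. A pharmacy preparation step appears in Table 1, and Data collection says "the serial number and dose of the pre-packaged iron infusion will be recorded in the template", so there are points at which an odd dose might be noticed. The article also condenses a fuller protocol, which may carry the right label. Finally, the 35% and 82% figures sit at the corners of an assumed weight range; at 70 kg the span is 40–72%.

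Much of this stands. It is probably a labelling slip, the intended dose can be recovered, no misdosing is shown, and whether the fuller protocol repeats the error cannot be known from the article. The thalassaemia minor figures rest on further assumptions and are secondary.

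It does not make the printed rule safe. The article states the formula in full, states it wrongly, and corrects it nowhere. None of the preparation or recording steps mentions a conversion. The hospital protocol is cited for how the iron is infused, not for how the dose is calculated. Study settings expects secondary sites to prepare and give the interventions as the protocol sets out, and the Hb value they would have in front of them is in g/dL.

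**Conclusion.** The concern holds. The dose rule for the experimental arm mixes g/L and g/dL and gives the wrong dose if followed as written. The excess is 40–72% at 70 kg and 35–82% over 45–120 kg, for Hb 5.5–8.0 g/dL. The weights are assumptions; the Hb range and constants are the protocol's. The claim is confined to literal application, and these ranges exclude women with thalassaemia minor, whose target differs and for whom the error can go either way. As a drug-dose rule, it must be corrected even though the intent can be inferred. The ferritin unit is a separate, minor label error and carries no weight in this conclusion.

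**What to change.** - Print the formula as dose (mg) = weight (kg) × (150 − Hb in g/L) × 0.24 + 500, or equivalently weight (kg) × (15.0 − Hb in g/dL) × 2.4 + 500.
- State that the adjusted target in thalassaemia minor must be in the same unit as the baseline Hb.
- Add a worked example: 70 kg, Hb 70 g/L (7.0 g/dL), 70 × 80 × 0.24 + 500 = 1844 mg.
- As a precaution, check any doses already prepared against the recorded weight, Hb and dose.
- Separately, correct the unit of the ferritin exclusion, presumably to microgram/L or ng/mL, with confirmation from the trial haematologist.

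The cost is a two-line correction, an example and a check of recorded doses. No extra patients are needed, and the sample size, endpoints and analysis are unaffected.

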### Outcomes

#### Primary outcomes

Hb, ferritn and CRP levels at Day 7

### Secondary outcomes

Hb, CRP, ferritin and reticulocyte count at Day 14 and 28clinical symptoms at day 7, 14 and 28breastfeeding quality at day 7, 14 and 28adverse reactions

Quantifying CRP will ensure changes to ferritin levels are not the result of an acute phase response. Reticulocyte count will be used as a marker of bone marrow response [19, 20].

### Statistics

To demonstrate equivalence of the interventions in restoring Hb levels at Day 7 with 90% power at 5% significance (α = 0.025), 116 women need to be recruited to each intervention group. Based on similar studies, this assumes an acceptable difference in Hb of 1 g/dL and an expected difference of 0.7 g/dL [2, 8, 12]. Hence, the final sample size, accounting for a 10% loss to follow up, is a total of 250 women.

Participants experiencing adverse reactions will remain in the trial unless they fail to meet inclusion and exclusion criteria at any point. Data will be analysed according to the intention to treat principle. Primary outcomes and secondary binary outcomes will be analysed using one sided and two group t-tests. The incidence of adverse reactions and symptom scores will be assessed by calculating rates and 95% confidence intervals. Validity of the Post Partum Symptom Scale (PPSS) will be determined at the time of analyses as part of an embedded study and if validated, correlations between subscales and primary outcomes will be analysed.

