**Discussion:**

If equivalence in Hb and ferritin levels, symptom scores and safety endpoints is demonstrated, intravenous iron may become the preferred treatment for women with acute post-partum anaemia to minimise transfusion reactions and costs.

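### The Day 7 Hb result is to be called equivalence, but the design supports only non-inferiority within 1 g/dL and may be sized for a significantly lower Hb with iron

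*Protocol article*

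**What the plan says.** The protocol article describes the Hb comparison in two ways.

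- **Non-inferiority.** The abstract's Methods/design paragraph, Primary objectives, Hypothesis (for Hb) and Design all call the trial, or its Hb question, non-inferiority. Under Statistics, the primary outcomes are "analysed using one sided and two group t-tests".
- **Equivalence.** The sizing sentence under Statistics gives its aim as equivalence of the two treatments on Day 7 Hb. The Discussion paragraph of the abstract states the conclusion in the same terms: "If equivalence in Hb and ferritin levels, symptom scores and safety endpoints is demonstrated, intravenous iron may become the preferred treatment".

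The sizing inputs under Statistics are "with 90% power at 5% significance (α = 0.025"), with the result that "116 women need to be recruited to each intervention group". The margin and the planning value are given together: "this assumes an acceptable difference in Hb of 1 g/dL and an expected difference of 0.7 g/dL". The section does not say which arm is expected to have the higher Hb, and it gives no SD.

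**The concern.** A one-sided non-inferiority test on Day 7 Hb supports one statement: Hb with iron is not lower by more than the margin. It does not show that the two treatments give the same Hb. Usually the difference in wording is minor. Here it may matter, because the planning value of 0.7 g/dL takes up 70% of the 1 g/dL margin. If it is the amount by which iron is expected to fall short, the scenario chosen for sizing is one in which the trial meets its criterion while showing that iron gives a lower Hb.

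The abstract makes equivalence on several endpoints the condition under which iron may become preferred. A reader told that Hb was equivalent, when the interval lay entirely on the side of lower Hb with iron, would be misinformed about the outcome on which the trial is sized.

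**Working it through.** **Inputs.** From Statistics: margin 1 g/dL, planning difference 0.7 g/dL, power 90%, α = 0.025 (taken as one-sided), 116 per arm. The SD is not stated and is back-solved below.

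**1. Reproducing 116 per arm.** The figure cannot be reproduced from the stated inputs alone. Reading 0.7 as an iron deficit leaves a distance to the margin of 1 - 0.7 = 0.3. From n = 2 × [SD × (1.960 + 1.282) / 0.3]²:

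SD = 0.3 × √(116/2) / 3.242 = 0.705 g/dL.

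With SD 0.70, the normal approximation gives 115 per arm, and the noncentral t calculation first reaches 90% power at 116 (0.9015). The stated figure therefore fits this reading.

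**2. Other readings of the 0.7.** The SD needed to give 116 per arm would be:

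- One-sided non-inferiority, no true difference: 1 × √58 / 3.242 = 2.35
- One-sided non-inferiority, iron better by 0.7: 1.7 × √58 / 3.242 = 3.99
- Superiority test for a 0.7 difference: 0.7 × √58 / 3.242 = 1.65
- Two one-sided tests within ±1, true difference 0: 2.11 to 2.32
- Symmetric ±1 test, difference of 0.7 in either direction: about 0.70, as in step 1

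**3. What success looks like at the planning value, taken as a deficit.**

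- SE = 0.705 × √(2/116) = 0.0925
- Half-width of the 95% interval = 1.96 × 0.0925 = 0.181
- Typical interval, iron minus transfusion = -0.7 ± 0.181 = -0.88 to -0.52
- Largest observed deficit that still passes = 1 - 0.181 = 0.82
- Smallest observed deficit whose interval excludes zero = 0.18

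Any observed deficit between 0.18 and 0.82 is both a success and a significantly lower Hb with iron.

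**4. Dependence on the true deficit** (SD 0.70, 116 per arm):

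| True deficit (g/dL) | P(success) | Share of successes with interval wholly below zero |
|---|---|---|
| 0 | about 1 | 2.5% |
| 0.1 | about 1 | 19% |
| 0.2 | about 1 | 58% |
| 0.3 | about 1 | 90% |
| 0.7 | 0.904 | essentially 100% |

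**5. Dependence on the SD** (true deficit 0.7, 116 per arm):

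| SD (g/dL) | Half-width | Largest passing deficit | P(success) | Share of successes with interval wholly below zero |
|---|---|---|---|---|
| 0.70 | 0.18 | 0.82 | 0.904 | essentially 100% |
| 1.0 | 0.257 | 0.743 | 0.627 | 99.9% |
| 1.5 | 0.386 | 0.614 | 0.331 | 83% |
| 2.0 | 0.515 | 0.485 | 0.207 | 0% |

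At SD 2.0 the half-width exceeds the largest passing deficit, so no result can be both. At SD 1.0 and above the trial no longer has its planned 90% power at this deficit.

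**The case against.** **A lower Hb within the margin is a valid non-inferiority result.** This stands. A significantly lower mean inside a pre-set margin does not make the trial's success wrong. The objection defends the term non-inferiority, however, and not the term equivalence, which the article uses in its sizing aim and its stated conclusion.

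**The direction of the 0.7 is not given.** This also stands. A reader might infer that a deficit is the only reading that leaves 0.3 of the margin. It is not: under a symmetric ±1 test, 0.7 in iron's favour leaves the same 0.3 and gives the same sample size. Background also cites an average iron gain of 2.5 g/dL at day 5. From entry Hb 8.0 that gives 10.5, above the transfusion target of 9.0; from 5.5 it gives 8.0, which is 1.0 below it. The deficit reading is favoured by the one-sided test and the non-inferiority objective, under which iron better by 0.7 would need an SD near 4. On the symmetric reading the planned interval would still exclude zero, on iron's side.

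**The margin.** A reader might infer that the margin gives away the whole benefit of transfusion, since red cells are "given to achieve a Hb of at least 9.0 g/dL" and 9.0 - 8.0 = 1.0. The documents do not support this. Entry Hb 8.0 is the top of the eligible range; at 7.5, 7.0 and 5.5 the margin is 67%, 50% and 29% of the minimum gain to 9.0. The 9.0 is a floor reached at transfusion, not a mean Day 7 effect against no treatment, whereas the margin applies to the Day 7 mean difference over all women. For the same reason, nothing here shows that a result at the margin could not be told apart from no benefit. The article attributes its sizing assumptions to similar studies, which are not available here.

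**Details belong in the SAP.** Interval reporting can properly sit there, and its absence from an article is no fault. The finding is about what the article states: a conclusion stronger than its test supports.

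**The abstract is cautious.** It says only that iron may become preferred, and requires ferritin, symptoms and safety as well as Hb. This limits the consequence but does not correct the Hb claim.

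**Conclusion.** The concern holds in a limited form. The article labels the Day 7 Hb conclusion equivalence, while its objective, design and one-sided test support only non-inferiority within 1 g/dL. That mismatch needs no assumption.

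Its practical size does. If the 0.7 g/dL is an iron deficit and the SD is about 0.70 g/dL, as 116 per arm implies, then observed deficits up to 0.82 pass and essentially every success in the design scenario has an interval wholly below zero. A reader might infer that any successful trial would show iron to be worse. That does not follow: at a true deficit of 0.2 it applies to 58% of successes, at 0 to 2.5%, and at SD 2.0 to none.

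The point should be corrected because it changes what the trial may claim. It is not a case against the margin or the sample size.

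**What to change.** Keep the margin and the sample size, and make three changes.

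1. In the Statistics sizing sentence and the abstract's Discussion paragraph, replace equivalence for Hb with the claim the test supports: Day 7 Hb with iron is not more than 1 g/dL lower than with RBC transfusion. Because the abstract's sentence also covers ferritin, symptoms and safety, word those separately according to what their own analyses can show.
2. State the direction of the expected 0.7 g/dL and the SD used. If that SD is not close to 0.70, or the direction is not a deficit, check that 116 per arm still follows.
3. Pre-specify, in the protocol or SAP, that the two-sided 95% confidence interval for the Day 7 Hb difference is reported. If it lies wholly below zero, the conclusion states that iron gave a lower Hb within the margin.

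The cost is a few sentences. No further data, visits or participants are needed, since Hb is already measured at entry and Day 7. The downside for the sponsor is a less favourable claim if the planning value proves correct.

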## Design

This is a multi-centre prospective, randomised, open-label, non-inferiority trial.

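### A total of 250 women does not cover a 10% loss on 116 per group: it covers about 7%, and 10% would need 258

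*Protocol article*

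**What the plan says.** All the figures are in the Statistics section of the protocol article. It asks for 116 women per intervention group, for 90% power at a 5% significance level that it glosses as α = 0.025. On the assumptions it says that "this assumes an acceptable difference in Hb of 1 g/dL and an expected difference of 0.7 g/dL", and it refers to similar studies for them. It then concludes: "Hence, the final sample size, accounting for a 10% loss to follow up, is a total of 250 women".

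The analysis sentence reads: "Primary outcomes and secondary binary outcomes will be analysed using one sided and two group t-tests". The Design section states: "This is a multi-centre prospective, randomised, open-label, non-inferiority trial". Allocation is 1:1 (Procedures, recruitment and randomisation). The article gives no SD for Day 7 haemoglobin and does not say which arm the expected 0.7 g/dL favours.

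**The concern.** The number needed per group, the loss allowed for and the total are printed together, and the last is presented as following from the other two. It does not. A reader who takes the paragraph at face value will believe that the trial keeps its 90% power if one woman in ten is lost by Day 7, when the stated total falls short of the stated requirement at that loss.

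At stake is the accuracy of a stated design property. If loss reaches the planned 10%, the trial will have fewer evaluable women than its own calculation requires, and the power quoted in later reports will be slightly too high.

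**Working it through.** **Inputs (Statistics, unless noted).** 116 per group; two groups, 1:1 (Procedures, recruitment and randomisation); loss 10%; total 250; margin 1 g/dL; expected difference 0.7 g/dL; one-sided α 0.025; power 90%. SD: not stated.

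**1. The plan's total.**
- Evaluable women required: 2 × 116 = 232.
- Inflation for 10% loss, N/(1 − d): 232/0.9 = 257.8, so 258 (129 per group).
- The cruder N × (1 + d): 232 × 1.1 = 255.2, so 256.
- Neither convention gives 250.

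**2. What 250 provides.**
- Women left after 10% loss: 250 × 0.9 = 225, or 112.5 per group. Shortfall: 232 − 225 = 7.
- Loss that still leaves 232: 1 − 232/250 = 18/250 = 7.2%.

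Steps 1 and 2 use only printed figures.

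**3. Reproducing 116 per group.** Take the 0.7 g/dL to lie towards the margin, so that the distance to it is 1 − 0.7 = 0.3 g/dL. Then

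SD = 0.3 × √(116/2) / (1.960 + 1.2816) = 0.705 g/dL.

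At SD 0.70 the normal formula gives 115 per group, and a t-test with 116 per group has 90.2% power. So 116 is a coherent result for an SD of about 0.70, and nothing here suggests that it is wrong.

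**4. Power after 10% loss.** Power = Φ(0.3 / (SD × √(2/n)) − 1.960).
- SD 0.705, n = 116: 90.0%. SD 0.705, n = 112.5: 89.1%.
- As a check with the t-test at SD 0.70: 89.1% for n = 112 and 89.4% for n = 113.

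**5. Does the size of the effect depend on the inferred SD?** Very little. If 116 per group gives exactly 90% under the sponsor's own inputs, the standardised distance is 1.960 + 1.2816 = 3.2416. With 112.5 per group it becomes 3.2416 × √(112.5/116) = 3.192, and Φ(3.192 − 1.960) = 89.1%, whatever the SD or the direction of the difference in a one-sided comparison. With assumed larger SDs and the same 0.3 g/dL, the drop from 116 to 112.5 per group is from 81.5% to 80.3% at SD 0.8, and from 62.7% to 61.4% at SD 1.0. The inflation slip costs about one percentage point in each case.

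**The case against.** The strongest reply is that nothing turns on this: 8 women in 258 and about one point of power will not change a trial's conclusion. That stands as a statement about size. It does not make the sentence correct, and the correction is free.

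A reader might go further and infer that the trial is underpowered because its calculation works only at an implausibly small, unstated SD. The documents do not support that.
- The document is a journal article that refers to similar studies for its assumptions. The SD may stand in the full protocol or in those studies, so its absence is not a finding.
- Power is at least 90% at any SD up to about 0.70, not only at that value, and the article offers no other SD to set against it. The lower power at SD 0.8 or 1.0 is arithmetic on assumed values.
- The back-solved SD depends on the direction of the 0.7 g/dL. If that difference favoured iron, a one-sided non-inferiority test would have 1.7 g/dL to the margin, and the same formula would give an SD of about 4.0 g/dL. For a two-sided equivalence claim, 0.3 g/dL is the binding distance either way.
- The entry criteria give a "resultant Hb drop of ≥3 g/dL and Hb of 5.5-8.0 g/dL", and a uniform spread over that window would have an SD of 2.5/√12 = 0.72 g/dL. This is no floor for the Day 7 SD. The uniform shape is an assumption, and both arms are treated according to baseline haemoglobin (Interventions): transfusion is guided by repeated checks towards a threshold, and the iron dose rises as haemoglobin falls. Either can narrow the spread by Day 7.

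**Conclusion.** The stated total is wrong as written: 250 women do not account for a 10% loss on 232. They cover 7.2%; a 10% loss needs 258. This rests on the article's own figures alone.

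The consequence is minor. At the planned loss 225 women remain, 7 fewer than required, and power is about 89% instead of 90%. That figure assumes that 116 per group gives 90% power on the sponsor's inputs, as it does at an SD near 0.70 g/dL with the expected difference lying towards the margin. The finding does not extend to the 116 per group, or to whether the underlying SD is realistic.

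**What to change.** Correct the closing sentence of the sample-size paragraph in one of two ways:
- state that 250 women randomised allows for about 7% loss to follow-up; or
- keep the 10% and state that about 225 women (112 per group) would then be evaluable, with power slightly below 90%. The figure is about 89% if the planning SD was near 0.70 g/dL.

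In either case, give the sponsor's own planning SD and say which arm the expected 0.7 g/dL favours, so that the power can be checked. The value of 0.70 g/dL is inferred here and should not be printed as the planning assumption unless the sponsor confirms it.

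The change is to wording only. No extra women are needed: going to 258 would restore consistency, but it would add 8 women for about one point of power. The only downside is a slightly less favourable stated figure.
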